#### Emergency Department (ED) visits

In the pilot data, there were an average of 15.5 ED visits per year in Veterans with care coordination. We estimated Veterans without care coordination to have 26 ED visits per year. With an estimated sample size and ED visit rates, we calculated 98.6% power to detect a difference of 20% in ED visits per year between those with and without care coordination, which is in line with prior studies (38).

#### Healthcare costs

We will estimate annual total healthcare costs (VA and Medicare), including outpatient, ED, UC, inpatient, and medication costs. For power calculation estimates, we rely on Yoon et al. (7), which indicates unadjusted VA costs for complex patients at $31,956 (95% CI $29,840, $34,443) in 2015 dollars. We estimated that we will have a minimum of 85.1% power to detect an effect size of 0.13–0.20 between Veterans with and without care coordination. We have considered the anticipated larger variance in costs expected as reported in prior research for cost estimations that include both VA and Medicare costs (1, 39, 40).

#### Mortality

We considered experience of Wang et al. (33), and our own preliminary analysis of primary care patients with risk scores indicating high-risk, in which yearly mortality rates ranged from 6.2% to 7.9%. Using data from VA and CMS mortality sources (41), conservatively, using a 5% mortality rate among Veterans with care coordination, we have 81% power to detect a significant odds ratio (OR) of 1.6, with power increasing to 88% if the mortality rate among Veterans without care coordination is 8%.

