#### Objective and study sample

We will characterize and compare the relationship between receiving care coordination services and subsequent healthcare use, health outcomes, and healthcare costs among Veterans with high-risk, high-need conditions in a prospective observational study. With existing data available in the VA's electronic health record (EHR), VA-purchased care claims, and Medicare claims data from the Centers for Medicare and Medicaid Services (CMS), we will identify and match Veterans with complex care needs with and without care coordination services based on clinical and sociodemographic characteristics and prior healthcare use. The VA lacks a standardized care needs assessment in the EHR, but does include a means to identify Veterans with high risk for hospitalization and/or mortality, based on annual care assessment of needs (CAN) scores (33). Those with a CAN score of 85 or greater, indicating their predicted probability for hospitalization and/or mortality at one-year is at or above the 85th percentile, will be included. The CAN score is generated from VA EHR data and includes information on sociodemographic characteristics, chronic illness measures (including the Deyo-Charlson comorbidity index), VA healthcare use, vital sign parameters, laboratory test values, specific medication use, and 18 drug interactions. The CAN score has been well validated for predicting hospitalization and mortality and is in wide use in the VA. Use of the CAN score allows us to identify those most likely to benefit from care coordination and explore the relationships with processes and outcomes. Exclusion criteria include CAN score less than 85 and missing data for key variables required for matching. We will follow Veterans with complex care needs, with and without care coordination services over time to examine and compare their healthcare use, costs, and health outcomes.

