#### Outcome measures

Pilot data from FY2018 from one VA medical center were used to estimate a conservative sample size of cases (those with a needs assessment documented) and comparator patients for at least 12 VA facilities. We estimated a minimum of 88 cases per site; and with a 1:1 match for comparators, a total sample of 2,112. With growth in the number of VA sites expanding and documenting care coordination services, we expect this number to be easily surpassed during the observation period (FY2019–FY2021).

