#### Analysis

We will describe and compare Veterans with complex care needs, with and without care coordination services along each outcome measure using descriptive statistics and visualizations including counts and proportions for categorical variables, and means, standard deviations, ranges, and quartiles for continuous variables, as well as 95% confidence intervals (CI) for all proportions and means. Unadjusted comparisons between the two groups will be tested using *t*-tests or Chi-squared tests. We will test the hypothesis that outcomes improved among Veterans with care coordination compared with Veterans without care coordination using regression models and an appropriate matching (e.g., propensity score matching) approach (42). As an observational study in which we are interested in assessing treatment effects, matching will allow us to compare outcomes for Veterans with and without care coordination services. Regression models planned include generalized linear mixed models (GLMM), logistic GLMM, and generalized estimated equations (GEE). Cost outcomes will be modeled with GEE to provide flexibility in choice of distribution and link function (43).

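### Aim 1 mortality is planned and powered as a yes/no outcome with no time-to-event method named, and the stated power does not follow from the stated inputs

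*Protocol article*

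**What the plan says.** All references are to Aim 1 of the protocol article.

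- **Mortality.** The background is that "yearly mortality rates ranged from 6.2% to 7.9" per cent. The power statement is built by "using a 5% mortality rate among Veterans with care coordination" and concludes that "we have 81% power to detect a significant odds ratio (OR) of 1.6". A second scenario assumes 8% mortality in the comparison group and states 88% power.
- **Analysis.** Unadjusted comparisons use t-tests or Chi-squared tests. For the adjusted work, "Regression models planned include generalized linear mixed models (GLMM), logistic GLMM, and generalized estimated equations (GEE"). Only cost is tied to a named model (GEE). The logistic GLMM is the model that most directly gives the odds ratio used for mortality.
- **Objective and study sample.** "We will follow Veterans with complex care needs, with and without care coordination services over time". The length of follow-up per Veteran is not given.
- **Outcome measures.** "We estimated a minimum of 88 cases per site; and with a 1:1 match for comparators, a total sample of 2,112". This is a floor: "we expect this number to be easily surpassed during the observation period (FY2019–FY2021").

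**The concern.** Death has a date, and the observation period spans three fiscal years. If Veterans enter at different times, they are observed for different lengths of time. A simple yes/no outcome cannot censor. It needs a common window, with short-follow-up Veterans dropped or counted as survivors and later deaths left out, or else it mixes unequal windows. An odds ratio also changes with the length of the window.

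Mortality is one of the hypothesised Aim 1 outcomes and has few events: about 135 deaths expected in 2,112 Veterans in one year under the article's own rates. A hazard analysis would use every observed death and handle unequal follow-up by censoring, on data the study already plans to hold. Separately, if the power figures are wrong, readers will misjudge how informative a null mortality result is.

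**Working it through.** **Inputs from the article.** 12 sites × 88 cases = 1,056 per group, 2,112 in total; 5% mortality with care coordination; OR 1.6, or 8% without care coordination; stated power 81% and 88%.

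**Assumptions.** Alpha 0.05 (stated only for Aim 2), two-sided unless noted; the 5% is a one-year risk, because the preceding rates are yearly; constant hazards; independent Veterans, with no allowance for site clustering or matching.

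**1. The article's own power figures.**
- OR 1.6 from 5%: odds = (0.05/0.95) × 1.6 = 0.0842, so risk = 0.0842/1.0842 = 7.77%.
- Two-proportion test, 5% vs 7.77%: difference 0.0277, standard error about 0.0106, ratio about 2.60. Power = Φ(2.60 − 1.96) ≈ 74.0%, against the stated 81%.
- 5% vs 8%: difference 0.030, standard error about 0.0107, ratio about 2.80. Power = Φ(2.80 − 1.96) ≈ 79.9%, against the stated 88%.
- One-sided, the results are 83.1% and 87.6%. This is the closest variant, off by 2.1 and 0.4 points. Adding a continuity correction gives 80.7% and 85.7%. No single variant tried gives both stated figures within 2 points.
- Two-sided, 81% needs about 1,256 per group and 88% about 1,326. At 1,256 per group the 8% scenario has about 86%, so the two figures also do not fit each other.

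**2. Time-to-event comparison for OR 1.6.**
- Hazards: −ln(0.95) = 0.0513 and −ln(1 − 0.0777) = 0.0809 per year; HR = 1.576, ln HR = 0.455.
- Schoenfeld: power = Φ(ln HR × √(D/4) − 1.96), where D is the number of deaths.

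| Follow-up | Deaths D | Log-rank power |
|---|---|---|
| Exactly 1 year | 135 | 75.2% |
| Uniform 0–3 years (mean 1.5) | 196 | 88.9% |
| Uniform 1–3 years (mean 2) | 259 | 95.6% |

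Worked row: 0.455 × √(196/4) ≈ 3.18; Φ(3.18 − 1.96) ≈ 0.889. Simulated log-rank tests (3,000 runs each) gave 75.2%, 88.9% and 95.1%. For 5% vs 8% the corresponding calculated values are 81.2%, 92.9% and 97.6%, against 79.9% for one-year yes/no.

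**3. Where the gain comes from.** At exactly one year the log-rank test adds 1.3 points over yes/no (75.2% vs 74.0%). With everyone followed for two years, yes/no has 95.2% and log-rank 95.7%. Nearly all the gain is therefore from longer follow-up. What the time-to-event model adds is the ability to use that follow-up when it differs between Veterans.

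**4. Sensitivity to a fading effect (simulation).** If the HR falls to 1.0 after year 1, log-rank power is 52% with two years for all and 47% with uniform 0–3 years, below the 74% of the one-year yes/no test. At a late HR of 1.25 it is 78% and 71%.

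**5. Sensitivity to sample size.** If the 29 sites named for Aim 2 each gave 88 cases (an assumption), there would be 29 × 88 = 2,552 per group. The one-year yes/no test for OR 1.6 would have about 98% power, leaving at most about 2 points to gain.

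**The case against.** A reader might infer that the plan throws away every death after month 12 and so gives up some 15–20 points of power. The article does not support that. It never says death is counted only within a year; the yearly rates are background to a power calculation. The list of models is open-ended, and a logistic GLMM on person-years would be a discrete-time survival model that uses later years. The mortality window and index date are details an article commonly leaves to the full protocol. The size of the gain rests on a follow-up length and a persistent effect that are not documented. A fading effect is plausible, since some of the services are tied to hospital discharge. A one-year horizon also fits the CAN score, which predicts one-year risk. And 2,112 is a stated minimum.

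Most of this stands, and it limits the claim to a conditional one. It does not remove the point. The article does name its tests, its models and its effect measure for mortality, and none is a time-to-event method. It describes no person-year structure. The stated 81% lies nearer to what one year per Veteran gives (74–75%) than to what 1.5 or 2 years would give (about 89% and 96%), so the planning figure does not appear to count multi-year follow-up. A larger sample would reduce the power gain but would not remove unequal follow-up.

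**Conclusion.** The point holds in a limited form. As written, mortality is a yes/no outcome summarised by an odds ratio, in a design where follow-up may well be unequal; a time-to-death analysis suits that better and costs little. The power gain is about 15 points with follow-up uniform over 0–3 years and about 22 points with 1–3 years, from the recomputed 74%. It requires 1,056 per group, two-sided alpha 0.05 and a hazard ratio that stays near 1.58. It is about 1 point if everyone has exactly one year, negative if the effect vanishes after year 1, and small if the sample is much larger than the minimum.

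The discrepancy in the stated power does not depend on follow-up: 81% and 88% do not follow from the stated rates and 1,056 per group at two-sided 0.05 (74.0% and 79.9%). A one-sided test would come close (83.1% and 87.6%), but the article does not state one.

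**What to change.** In the Aim 1 mortality and analysis sections:

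1. Make the mortality analysis time to death from the matched index date, using a Cox model with a facility frailty or a cluster-robust variance that respects the matching. Censor at the end of the mortality data and report a hazard ratio.
2. Report the one-year Kaplan-Meier risk difference alongside. It covers the case where the effect wanes or hazards are not proportional, and keeps the link to the one-year CAN horizon.
3. State the follow-up window for mortality.
4. Restate the mortality power as a hazard ratio with the expected number of deaths, alpha, sidedness and the sample size used, and correct or explain the 81% and 88%.

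The cost is wording, one different model and a recalculation. No new Veterans, data or procedures are needed, provided the VA and CMS mortality sources give death dates.

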Measures for analysis will be constructed from the six dimensions of the validated questionnaire items of the PPIC 2.1. Additional validated items will verify provider attribution, measure potential differences in individual tendency to give more positive or negative responses using the standardized life orientation test-revised (LOT-R) scale (45), and provide information about Veterans’ sociodemographic characteristics. Surveys will be linked with existing VA and CMS data to verify or ascertain Veterans’ sociodemographic characteristics, and to ascertain their clinical characteristics and healthcare use, including use of care coordination services.

To account for clustering by VA site, we considered an intra-class correlation coefficient of 0.01. Previous work by Benzer et al. (46) using an adaptation of the PPIC instrument on a cohort of Veterans reported mean scores [standard deviation (SD)] in the dimensions of: knowledge integration 3.18 (SD 0.83), support for self-care 3.00 (SD 0.85), and staff knowledge 3.02 (SD 0.91). For our target sample size, we have over 96% power to detect a significant difference between group means as low as 0.3, assuming a maximum SD of 0.9. Power analyses used alpha = 0.05 and were conducted in PASS v16.0.5.62 (47).

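### At the stated minimum of 2,112 Veterans and 5% mortality, two-sided power for mortality is about 74% and 80%, not the printed 81% and 88%

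*Protocol article*

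**What the plan says.** All places are in the protocol article, Aim 1 unless noted.

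- **Sample size (Outcome measures).** "We estimated a minimum of 88 cases per site; and with a 1:1 match for comparators, a total sample of 2,112". This refers to cases and "comparator patients for at least 12 VA facilities". The article adds that "we expect this number to be easily surpassed during the observation period (FY2019–FY2021"; no larger number is given.
- **Mortality.** Yearly mortality in high-risk patients is reported as 6.2% to 7.9%. The calculation is then made, as a conservative choice, "using a 5% mortality rate among Veterans with care coordination". The result is "we have 81% power to detect a significant odds ratio (OR) of 1.6, with power increasing to 88" per cent if mortality without care coordination is 8%. The paragraph gives no sample size, alpha, sidedness or test.
- **Healthcare costs.** Power of at least 85.1% is stated for standardised effects of 0.13 to 0.20.
- **Alpha.** The only statement is under Aim 2, Measures: "Power analyses used alpha = 0.05". Sidedness is not given there either.
- **Analysis.** Unadjusted comparisons use t-tests or chi-squared tests with 95% confidence intervals; adjusted models follow matching.

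**The concern.** Decreased mortality is one of the named Aim 1 hypotheses, and the text presents it as having more than 80% power under a cautious event rate. If the printed powers do not follow from the printed inputs, a reader will take the minimum sample to be better able to detect the stated odds ratio than it is. At that sample the chance of missing the effect would be 26% rather than 19% in the first scenario, and 20% rather than 12% in the second. That bears on how a null mortality result is read.

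**Working it through.** **Inputs**

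- n = 2,112 / 2 = 1,056 per group (12 sites × 88 cases, matched 1:1; Outcome measures).
- p1 = 0.05 with care coordination (Mortality).
- Scenario 1: OR 1.6. p2 = (0.05 × 1.6) / (0.95 + 0.05 × 1.6) = 0.08 / 1.03 = 0.0777.
- Scenario 2: p2 = 0.08, which is an OR of (0.08/0.92) / (0.05/0.95) = 1.65.
- Alpha 0.05, two-sided: an assumption, tested first.

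**Which convention does the article use?** The cost power can be checked on the same sample. Power = Φ(d√(n/2) − z), with d = 0.13 and √(1,056/2) = 22.98, so d√(n/2) = 2.987.

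- Two-sided: Φ(2.987 − 1.960) = Φ(1.027) = 84.8%. The article states 85.1%.
- One-sided: Φ(2.987 − 1.645) = Φ(1.342) = 91.0%.

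So 1,056 per group with a two-sided test gives the cost figure closely; a one-sided test does not.

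**Mortality power.** With p̄ the mean of the two rates:

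Power = Φ{[(p2 − p1) − 1.960 × √(2p̄(1 − p̄)/n)] / √([p1(1 − p1) + p2(1 − p2)]/n)}

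- Scenario 1: difference 0.02767, p̄ = 0.06383, null SE 0.01064, alternative SE 0.01062. Φ[(0.02767 − 0.02085)/0.01062] = Φ(0.642) = **74.0%** (stated 81%).
- Scenario 2: difference 0.03, p̄ = 0.065, null SE 0.01073, alternative SE 0.01071. Φ[(0.03 − 0.02103)/0.01071] = Φ(0.838) = **79.9%** (stated 88%).

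**Does the choice of test explain the gap?** Two-sided, unpaired, 1,056 per group:

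| Test | OR 1.6 | 5% vs 8% |
|---|---|---|
| Pooled | 74.0% | 79.9% |
| Unpooled | 74.1% | 80.0% |
| Log-odds Wald | 73.3% | 79.2% |
| Arcsine | 74.4% | 80.4% |
| Continuity-corrected | 71.0% | 77.3% |
| Chi-squared, simulated | 74.4% | 80.4% |
| Stated | 81% | 88% |

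None of these reaches either stated value.

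**Do other inputs give the stated pair?**

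- One-sided 0.05, pooled: 83.1% and 87.6%. The second rounds to 88%; the first is two points off.
- Larger sample, two-sided pooled: 81% needs 1,256 per group (2,512 in all) in scenario 1, and 88% needs 1,326 per group (2,652 in all) in scenario 2. At 1,320 per group the pair is 82.9% and 87.9%. A power rounding to 81% in scenario 1 needs about 1,240 to 1,272 per group, and one rounding to 88% in scenario 2 about 1,305 to 1,346. The ranges do not overlap, so no single sample size gives both figures.
- Matched-pair (McNemar) test with a within-pair correlation of 0.2, a value the article does not give: 82.6% and 87.6%.

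**The case against.** The mortality paragraph names no sample size, alpha, sidedness or test, and a journal article commonly leaves such settings to the full protocol. The hypothesis is directional, and a one-sided test comes within about two points of both figures. A sample of about 1,320 per group also comes close, and 2,112 is expressly a minimum. On this view the fault may be an undisclosed setting rather than a wrong number.

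Part of this stands. The two-sided convention is inferred, and the mortality calculation may have used something else. But 2,112 is the only Aim 1 sample size stated and it heads the same subsection, the cost power fits 1,056 per group two-sided, and no one-sided test is mentioned anywhere. Neither alternative reproduces both printed figures exactly. Either way the paragraph needs correcting or completing.

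Three stronger readings are tempting but unsupported:

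- *That the study is underpowered for mortality.* Aim 1 uses existing data from all VA facilities offering these services, and the minimum is expected to be exceeded. Aim 2 mentions 29 sites with active programmes. If 88 cases per site held at all of them (an assumption), there would be 29 × 88 = 2,552 per group and power of about 98% and 99%.
- *That clustering by site must lower power further.* Exposure can vary within site and comparators are matched, so precision need not fall; the article does not settle it.
- *That the figures were really computed at baselines of 6.2% and 7.9%.* With OR 1.6 those give about 82% and 89%, not 81% and 88%, and the text assigns 5% to Veterans with care coordination and 8% to those without. This is a guess.

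**Conclusion.** The concern holds for the printed figures at the stated minimum sample. With 1,056 per group, 5% mortality under care coordination and an unpaired two-sided test at 0.05, power is about 74% for OR 1.6 and about 80% for 5% against 8%. The article overstates these by about 7 and 8 points. The conclusion rests on two assumptions: that the mortality power refers to 2,112, and that it used the convention that fits the cost power. It concerns a stated power at a minimum sample, not the power the study will finally have, which may be higher.

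**What to change.** Restate the result in the Mortality paragraph along these lines: with the minimum of 1,056 per group, two-sided alpha 0.05 and 5% mortality with care coordination, power is 74% for an odds ratio of 1.6 (7.8% without care coordination) and 80% for 8% without care coordination (odds ratio 1.65).

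If a larger sample, a one-sided test or a paired test was actually used, state the sample size, alpha, sidedness and test (and the within-pair correlation if paired), and give the powers those settings yield. For reference, 81% and 88% two-sided need about 1,256 and 1,326 per group respectively. The paragraph can add that 2,112 is a minimum and that realised power may be higher. The figures should not be reattributed to the 6.2% and 7.9% rates unless the authors' own calculation shows that those were the inputs.

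The cost is wording only, with a less favourable power at the minimum sample. No enrolment, analysis or decision rule changes.

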#### Analysis

We will describe and compare Veterans with complex care needs, with and without care coordination services along each outcome measure using descriptive statistics and visualizations including counts and proportions for categorical variables, and means, standard deviations, ranges, and quartiles for continuous variables, as well as 95% confidence intervals (CI) for all proportions and means. Unadjusted comparisons between the two groups will be tested using *t*-tests or Chi-squared tests. We will test the hypothesis that outcomes improved among Veterans with care coordination compared with Veterans without care coordination using regression models and an appropriate matching (e.g., propensity score matching) approach (42). As an observational study in which we are interested in assessing treatment effects, matching will allow us to compare outcomes for Veterans with and without care coordination services. Regression models planned include generalized linear mixed models (GLMM), logistic GLMM, and generalized estimated equations (GEE). Cost outcomes will be modeled with GEE to provide flexibility in choice of distribution and link function (43).

### Aim 2: Veterans' perspectives

#### Research question and hypotheses

For Aim 2, the main research question is “Are care coordination services associated with differences in perceived care integration and patient centeredness of care among Veterans with complex care needs? We hypothesize that Veterans with high-risk, high-need conditions with complex care needs who receive care coordination services will report greater levels of care integration and patient-centeredness than those who do not receive these services.

